The efficacy of albendazole is variable against *Trichuris trichiura* compared to other anthelmintics; the cure rate ranges between 2.6 and 64.5% [8] and the egg reduction rate ranges between 7 and 83.1%. However, high cure rates of *Trichuris trichiura* are observed in some contexts [9–11]. In a study conducted in the Peruvian Amazon, an open-pair randomized trial was conducted in fifth-grade children from 18 primary schools (9 intervention and 9 control). Intensity of *Ascaris lumbricoides* infection at follow-up was 58% lower in children from intervention schools, a significant reduction as compared to children from control schools (RR = 0.42; 95% CI 0.21 to 0.85), but no significant changes were observed in the intensity of hookworm or *Trichuris trichiura* [12]. In another study from Peru, a total of 1193 school-age children were dewormed with a single dose of Albendazole (400 mg). Of the 909 children who tested positive for at least one STH infection, a random sample of 385 were followed up 2 weeks later with a second stool sample. The efficacy of albendazole was variable, with an egg reduction rate of 99.8% for *Ascaris lumbricoides* (95% CI 99.3–100); 93.6% for hookworm (95% CI 88.2–96.6), and 72.7% for *Trichuris trichiura* (95% CI 58.5–79, 1) [13]. In many cases treatment with albendazole alone appeared inadequate, especially for *Trichuris trichiura*. Other interventions such as combined therapy have been evaluated in other contexts. Ivermectin results in higher cure rates than albendazole and is well tolerated. The benefits of ivermectin for helminth infections would depend on the amount of resistance present [14–16].

Large-scale interventions to control soil-transmitted helminth infections at the community level with anthelmintic drugs such as albendazole have the potential to exert selective pressures which may favor the development of drug resistance, which could significantly reduce the benefits provided by deworming programs. Drug resistance in parasitic nematodes is caused by a single nucleotide polymorphism (SNP) in the β-tubulin gene at codon positions 200 (T → A), 167 (T → A) or 198 (A → C) [17].

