### Sample size

Sampling will be carried out throughout the jurisdiction of the 6 de Octubre Health Center, which includes rural, peri-urban and urban areas, with a total potential study population of 3379 children ages 2 to 11 years based on health center databases. Based on this study population of 3379 children aged 2 to 11 years, to measure clinical resistance to albendazole a sample of 380 children was needed. This calculation was made in Epi Info Version 7.2 applying a type I error of 5% and assuming 50% prevalence of helminths in children, 25% frequency of *Trichuris trichiura* in children with helminths, 50% resistance to albendazole based on detection of any helminth in a follow-up sample and adjusting for 10% loss to follow-up for study participants.

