Direct observation: In a properly labeled slide, 0.5 g of feces will be applied with a wooden applicator and 20 µL of saline solution will be added. The first observation will be made from left to right, then the procedure will be repeated with 20 µL of Lugol’s solution added. Both observations will be made with the 10× and 40× objectives in order to qualitatively identify the absence or presence of helminths (*Ascaris lumbricoides*, *Trichuris trichiura*, hookworms, and *Strongyloides stercoralis*).Kato-Katz method: Two grams of feces will be placed on a smooth and sterile surface, covered with a piece of nylon and pressed with a flat-edge plastic applicator. The filtered feces will then be placed in the center of a 41.7 mg template on a slide until the hole is filled, after which the template will be removed and the sample will be covered with a cellophane sheet previously imbued in a glycerol-blue solution of methylene, and pressure will be applied until the sample is distributed homogeneously. After a 30-min incubation, eggs counts will be carried out using the 10× objective and a cell counter, the total number of eggs counts per species will be reported in eggs per gram (epg) and will be multiplied by 24 (41.7 mg template) [27], and the results of each parasite found will be recorded and reported quantitatively. This procedure will be performed on the 4 samples per subject collected throughout the study [28].STH infection by qPCR: To measure the intensity of the infection, quantitative polymerase chain reaction (qPCR) will be used in such a way that the Kato-Katz variability between users is reduced and the sensitivity of the detection of low-grade parasitic infections is increased [29, 30]. Real-time multiplex qPCR will be performed on positive samples (Day 0) for helminths that were identified by direct observation and Kato-Katz for the simultaneous detection of *Ascaris lumbricoides*, *Trichuris trichiura*, *Necator americanus*, *Ancylostoma duodenale*, and *Strongyloides stercoralis* [31]. If the sample from Day 0 is negative, the sample from Day 15 will be analyzed if it is positive for helminths. Amplification will be performed in a Quant Studio 7 Flex thermocycler (Applied biosystems) in a total volume of 25 µL using GoTaq® qPCR Probe Master Mix (Promega, USA) and 5 µL of fecal DNA. There will be two multiplex qPCR assays (STH1 and STH2); STH1 will be used to detect *Ascaris lumbricoides*, *Trichuris trichiura* and *Strongyloides stercoralis*, while STH2 will be used for the 3 species of hookworms. The cycling conditions for both cases will be the following: 1 cycle at 95 °C for 5 min, 40 cycles at 95 °C for 10 s and 1 cycle at 60 °C for 60 s. The primers will be the same ones used by Azzopardi et al. [32] which can be seen in Table 1.**Table 1 Tab1:** Primers used in multiplex qPCR analysis of stool samples by STH1 and STH2

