### Statistical analysis

Data will be analyzed in Access using Stata, using chi square, Fisher’s exact, and Wilcoxon tests to compare frequencies between groups. To analyze the data from direct observation and quantification by the Kato-Katz method, descriptive statistics will be used, to report the prevalence found in percentages. For the sociodemographic and clinical data of the study population, measures of central tendency and dispersion will be used for the quantitative variables and measures of relative frequency for the qualitative variables. Comparisons will also be made between sample 1, sample 2, sample 3 and sample 4 to determine the positivity of each species of parasite found using the Yates chi-square test, setting a significance level of p < 0.05.

The sociodemographic variables will be compared with the parasite load and presence/absence of parasites, using a multiple logistic regression model (univariate t-test), to determine the variables statistically associated with infection by *Ascaris lumbricoides*, *Trichuris trichiura* and hookworms.

The quantification performed with the Kato-Katz method will be compared with the Ct value (Ct threshold) of the multiplex qPCR, by converting Log10 of the absolute egg count per stool sample, in order to estimate the absolute egg counts in eggs per gram (EPG) in the DNA extractions, using the following formula [33]:$${\text{EPG}}\;{\text{Ascaris}} = 10\left( {{\text{Ct}} - 36.97} \right)/ - 3.489,$$$${\text{EPG}}\;{\text{Trichuris}} = 10\left( {{\text{Ct}} - 36.73} \right)/ - 3.288,$$$${\text{EPG}}\;N.\;americanus = 10\left( {{\text{Ct}} - 35.02} \right)/ - 3.641,$$$${\text{EPG}}\;A.\;duodenale = 10\left( {{\text{Ct}} - 35.02} \right)/ - 3.641.$$

To determine treatment efficacy, the prevalence will be measured before and after receiving treatment and compared using the Yates chi-square test. For calculations of cure rate and intensity of infection obtained from qPCR, only data from positive results before taking the first dose will be included [34].

The cure rate will be measured using the following formula:$$\frac{{\# \;{\text{positive}}\;{\text{for}}\;{\text{helminths}}\;\left( {{\text{pretreatment}}} \right) - \# \;{\text{negative}}\;{\text{for}}\;{\text{helminths}}\;\left( {{\text{post}}\;{\text{treatment}}} \right)}}{{\# \;{\text{cases}}\;{\text{positive}}\;{\text{for}}\;{\text{helminths}}\;\left( {{\text{pretreatment}}} \right)}} \times 100.$$

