Intensity of infection will be measured using the following formula:$$\frac{{{\text{mean}}\;{\text{egg}}\;{\text{count}}\;\left( {{\text{pretreatment}}} \right) - {\text{mean}}\;{\text{egg}}\;{\text{count}}\;\left( {{\text{post}}\;{\text{treatment}}} \right)}}{{{\text{mean}}\;{\text{egg}}\;{\text{count}}\;\left( {{\text{pretreatment}}} \right)}} \times 100.$$

And the calculation of the rate of reduction of eggs by helminth species:$$\frac{{\left[ {1 - {\text{mean}}\;{\text{egg}}\;{\text{count}}\;{\text{in}}\;{\text{EPG}}\;\left( {{\text{post}}\;{\text{treatment}}} \right)} \right]}}{{{\text{mean}}\;{\text{egg}}\;{\text{count}}\;{\text{in}}\;{\text{EPG}}\;\left( {{\text{pretreatment}}} \right)}} \times 100.$$

In addition, a comparison of the cycle threshold (Ct) by qPCR will be made using the Student’s t-test for paired samples.

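### The named efficacy test uses only presence or absence of helminths, and the paired egg counts are merely described, so a large fall in Trichuris eggs can go undetected

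*Protocol article*

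**What the plan says.** All references are to the protocol article.

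- **Efficacy test** (Statistical analysis): "To determine treatment efficacy, the prevalence will be measured before and after receiving treatment and compared using the Yates chi-square test". Positivity by species is also compared across the four samples "using the Yates chi-square test, setting a significance level of p < 0.05".
- **Egg counts** (Laboratory analysis): Kato-Katz gives EPG per species, and "This procedure will be performed on the 4 samples per subject collected throughout the study".
- **Use of the counts** (Statistical analysis): direct-observation and Kato-Katz data are to be described and reported as percentages positive. Egg reduction appears as a formula ("And the calculation of the rate of reduction of eggs by helminth species"), with no interval or test. Wilcoxon tests are named, but for frequencies between groups.
- **Ct test** (Statistical analysis): a paired t-test compares Ct values.
- **Expected response** (Background): for Trichuris "the cure rate ranges between 2.6 and 64.5" percent, and one Peruvian study found an egg reduction of 72.7%.

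**The concern.** Albendazole can cut egg output sharply while leaving many children positive. A comparison of percentages positive does not register that change. Trichuris is where this matters most: the Background describes albendazole as variable against it, and only about one child in eight is assumed to carry it. The study could therefore report a non-significant efficacy test for Trichuris beside a large fall in eggs, with no measure of how precisely that fall was estimated. The Discussion says that results of such studies may lead to guidelines being re-evaluated.

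**Working it through.** **1. The plan's own sample size.** Inputs from Sample size: N = 3379, p = 0.50, type I error 5%. Assumed, because not stated: half-width d = 0.05.

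n = N·p·q / [(d/1.96)²·(N − 1) + p·q] = 345.0; 345 × 1.10 = 379.5, so 380. The ten age strata under Recruitment also sum to 345. The stated figure reproduces.

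**2. Trichuris-positive children.** Sample size gives 50% × 25% = 12.5%, with 10% loss.

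- From 380: 380 × 0.9 = 342 followed; × 0.125 = 42.75, about 43.
- From 345: 345 × 0.9 = 310.5, about 311 followed; × 0.125 = 38.8, about 39.

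**3. Cures needed by the stated test.** Yates χ² = T(|ad − bc| − T/2)² / [(a+b)(c+d)(a+c)(b+d)]. With 43 of 342 positive before and 26 of 342 after (17 net cures), T = 684 and |ad − bc| = 43·316 − 299·26 = 5814, so χ² = 684 × 5472² / (342 × 342 × 69 × 615) = 4.13, p = 0.042. With 16 cures χ² = 3.58, p = 0.058. The threshold is 17 of 43 (39.5%). With 39 of 311, 16 cures give p = 0.045 and 15 give p = 0.063, so the threshold is 16 of 39 (41.0%).

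Power with 43 positives is the binomial chance of 17 or more cures, assuming no new positives:

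| Observed cure rate | 2.6% | 20% | 30% | 40% | 50% | 64.5% |
|---|---|---|---|---|---|---|
| Power | 0.00 | 0.003 | 0.12 | 0.58 | 0.94 | 1.00 |

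If the test were restricted to baseline positives, which the text does not say for prevalence, 6 of 43 would suffice: power 0.001 at a 2.6% cure rate, 0.26 at 10% and 0.89 at 20%.

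**4. What the counts add.** Simulated power for a 72.7% mean egg reduction. Assumed: gamma EPG with shape 0.5 and mean 300 to 3000, day-to-day gamma variation with shape 1 or 2, Poisson slide counts at EPG/24, 400 to 500 runs per scenario.

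| True clearance (infected children) | Yates | Exact McNemar | Signed-rank on counts |
|---|---|---|---|
| 0–10% (39) | 0–14% | 9–86% | 99–100% |
| 0–10% (43) | 0–8% | 7–67% | 97–100% |
| 25% (39) | 11–52% | 93–99% | 99–100% |
| 50% (39) | 90–95% | at least 99.8% | at least 98.6% |
| 50% (43) | 83–93% | at least 96% | at least 96% |

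A separate repeat at 0–10% clearance gave 0–4%, 9–64% and 94–100%. Observed cure exceeds true clearance (about 9–39% observed at 0–10% true), because a light infection can give an empty slide.

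**5. Whether the Ct test fills the gap.** Laboratory analysis runs qPCR on positive day 0 samples, and on the day 15 sample when day 0 was negative. That yields no pair. The Abstract, and an earlier paragraph of Laboratory analysis, run it on positive second samples, so pairs exist only in children not cured. A 72.7% fall corresponds to a Ct shift of 3.288 × log10(1/0.273) = 1.85. With 26 to 32 such pairs and an assumed SD of 5 down to 2, power would be 0.44 to 1.00, but only if the pairs exist.

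**6. The printed egg-reduction formula.** It subtracts the post-treatment mean from 1 before dividing. For 500 falling to 136.5 EPG it gives (1 − 136.5)/500 × 100 = −27.1. The separate intensity formula gives (500 − 136.5)/500 × 100 = 72.7.

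**The case against.** **Intensity is tested.** The article chooses qPCR for intensity in order to reduce between-reader variability, and plans a paired test on Ct. It is therefore wrong to say that no paired comparison of intensity is planned. What survives is narrower: that test is not on egg counts, is not the one named for efficacy, and lacks usable pairs or leaves out cured children.

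**Positivity is the stated outcome.** Sample size and Laboratory analysis define clinical resistance by finding helminths at follow-up. A reader might infer that a non-significant Yates test would be declared no effect or taken as resistance. The document contains no such rule. Nor are the counts discarded: egg reduction is to be calculated, so a fall would be visible. This stands, and it is why prevalence and cure rate should stay.

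**An article may leave intervals to the analysis plan.** That is fair for the missing interval alone. But this article itself fixes the scale on which efficacy is determined and assigns the counts to description.

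**Much of the loss comes from ignoring pairing.** This is largely right. At 25% or more true clearance, a paired positivity test recovers most of the power. The low-clearance scenario also joins a cure-rate range from one source to an egg reduction from another study, for which no Trichuris cure rate is given.

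**A signed-rank test is a poor lead analysis.** This also stands. Its null is zero change, and a 50% egg reduction already gives about 100% power, so significance would not separate good from much-reduced efficacy. Its rejection rate with no drug effect was 4–7% in most settings. It rose to 14% with stronger day-to-day variation (shape 0.5, mean 300) among baseline positives. It reached 19–28% in a model that selected baseline positives and gave each child a skewed response with mean 1.

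**Conclusion.** The point holds in this limited form. The only test named for efficacy is an unpaired comparison of prevalence, and the Kato-Katz counts carry no inference. For Trichuris the test is non-significant unless about 40% of infected children are cured, which leaves much of the cited 2.6 to 64.5% range where a large egg reduction can be missed. That threshold follows from the plan's inputs, given no new positives at follow-up and the test applied to all followed children.

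The further advantage of counts over a paired positivity test is confined mainly to true clearance of about 0 to 10%. Its size depends on the assumed EPG means and dispersions and on pairing a 72.7% reduction with low clearance. At 50% clearance the stated test would usually be significant. The documents do not support the stronger readings that intensity goes untested altogether or that a non-significant result would be called resistance.

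**What to change.** In Statistical analysis:

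- Make the species-specific egg reduction rate the lead efficacy estimate for Ascaris, Trichuris and hookworm. Calculate it from paired day 0 and day 15–25 Kato-Katz counts, with a 95% bootstrap interval that resamples children so that pairs stay together.
- State the population: children positive for that species at baseline, with all children who have both samples as a sensitivity analysis.
- Correct the bracketing of the egg-reduction formula to (1 − post/pre) × 100.
- Keep a signed-rank test on the paired counts as supporting only.
- Keep cure rate and prevalence alongside, because resistance is defined by positivity.

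The cost is analysis wording and a few lines of Stata; all counts are already collected. There are small downsides. Selecting baseline positives brings some regression to the mean, which the sensitivity analysis helps to show, and with about 40 children the Trichuris interval will be wide.

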### Study design (see Fig. 1)

**Fig. 1 Fig1:**
[figure not shown]
Study design

Prospective cohort study of children aged 2 to 11 years, with an individual time of participation of 4 and a half months.

Participants will be boys and girls ages 2 to 11 years who live in the catchment area of the Centro de Salud 6 de Octubre, located in the district of Belén, city of Iquitos, and department of Loreto in Peru.

Inclusion criteria:Parental written informed consent, in addition to the verbal and written assent for children ages 6 to 11 years.No antiparasitic treatment in the prior 3 months [18].Permanent residence in the study community, with no plans to move in the next 6 months.

Major outcomes:Albendazole resistance of intestinal helminths (Trichuriasis, Ascariasis, Hookworm, Strongyloides).Reinfection with intestinal helminths 4 months after treatment with Albendazole.

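### The test named to determine efficacy asks only whether prevalence changed; for any helminth it is significant from 5% to about 84% treatment failure, so it cannot answer the resistance question

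*Protocol article*

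**What the plan says.** All references are to the protocol article.

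- **Study design** lists as the first major outcome "Albendazole resistance of intestinal helminths".
- **Sample size** states that "to measure clinical resistance to albendazole a sample of 380 children was needed", and the calculation assumes "50% resistance to albendazole based on detection of any helminth in a follow-up sample".
- **Statistical analysis** gives the efficacy method: "To determine treatment efficacy, the prevalence will be measured before and after receiving treatment and compared using the Yates chi-square test". Shortly before, the same section compares species positivity across the four samples "using the Yates chi-square test, setting a significance level of p < 0.05". I take the 0.05 level to apply to the efficacy comparison as well.
- The same section then gives formulas for a cure rate, a relative change in mean egg count (labelled intensity of infection) and an egg reduction rate by species. It restricts the cure rate and the qPCR intensity to children positive before the first dose. The article attaches no reference value to any of these for judging efficacy or resistance.

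**The concern.** The null hypothesis of the named test is equal prevalence before and after albendazole, that is, a drug with no net effect. Rejecting it shows that some children cleared their infection. The study asks something else: in what share of infected children did treatment fail? A drug that fails in half of them still halves the prevalence, and a test of no change detects a halving easily.

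Pairing is a separate matter. The samples come from the same children and the Yates test treats them as independent, but a correctly paired test of the same null would answer the same unhelpful question.

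The Discussion says the data should allow clinical guidelines to be re-evaluated. A small p-value offered as the determination of efficacy could point that re-evaluation the wrong way while half of infected children remained positive.

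**Working it through.** **Inputs from the Sample size section**

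- Population of 3379 and sample of 380.
- Two-sided error rate of 5%, and half of all children infected at baseline.
- Trichuris present in a quarter (25%) of the infected.
- Treatment failure in half of the infected.
- An allowance of 10% for children lost.

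**Step 1. Reproduce the plan's sample size.** The single-proportion formula with finite population correction is n = N·p·q / [(d²/z²)(N − 1) + p·q]. With N = 3379, p = q = 0.50, z = 1.96 and d = 0.05 it gives 345. The precision d is not stated and is my assumption. The age strata under Recruitment of participants also sum to 345, and 345 × 1.10 = 379.5, which rounds to 380. I use 345 as the number followed; 380 less 10% is 342, and the results are practically the same.

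**Step 2. Any helminth.** Baseline positives: 345 × 0.50 ≈ 172. With a, b positive and negative before, c, d positive and negative after, and N = 690 samples, the Yates statistic is

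N(|ad − bc| − N/2)² / [(a+b)(c+d)(a+c)(b+d)].

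At 50% failure, a = 172, b = 173, c = 86, d = 259:

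690 × (|44548 − 14878| − 345)² / (345 × 345 × 258 × 432) = 44.7, p = 2.3e-11.

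Other failure rates, with no new positives:

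| Failure | Positive before v after, of 345 | Yates chi-square | p |
|---|---|---|---|
| 5% | 172 v 9 | 196.6 | 1e-44 |
| 50% | 172 v 86 | 44.7 | 2.3e-11 |
| 84% | 172 v 145 | 3.94 | 0.047 |

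One more failure (172 v 146) gives p = 0.056. With all 380 children followed, the boundary is about 85% (190 v 162, p = 0.0495).

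New positives do not change this at 50% failure. If 5%, 10% or 20% of baseline negatives turn positive (assumed; the article gives no rate), p is 3e-9, 2e-7 and 1e-4.

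**Step 3. Trichuris.** Baseline positives: 345 × 0.50 × 0.25 ≈ 43, leaving 302 negative. At 50% failure, 43 v 21.5 gives chi-square 7.2, p = 0.007, and 43 v 22 gives 6.8, p = 0.009. If 2% of the 302 turn positive (about 6), 43 v 27.5 gives p = 0.07 and 43 v 28 gives p = 0.08. At 5%, 43 v 37 gives p = 0.55.

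**Step 4. Pairing.** An exact paired test for Trichuris with 21 children clearing and none newly positive gives p = 2 × 0.5²¹ ≈ 1e-6. Pairing sharpens the test of no change and leaves the question unchanged.

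**Step 5. What estimation gives.** Wilson 95% intervals for 50% failure are 43% to 57% with 172 infected children and 36% to 64% with 43.

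**Step 6. The printed formulas.** The cure-rate numerator subtracts post-treatment negatives from pre-treatment positives. With 163 of 172 cured it gives (172 − 163)/172 = 5%, which is the failure rate; the cure rate is 163/172 = 95%. At exactly 50% the two coincide, which hides the error. The egg reduction formula places the 1 inside the numerator, (1 − post)/pre, so it is negative whenever the post-treatment mean exceeds 1 egg per gram. The formula labelled intensity of infection, (pre − post)/pre, is algebraically the correct egg reduction.

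**The case against.** The strongest reply is that the article does more than run this test.

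- Prevalence is measured before and after, so both percentages will be visible.
- A cure rate and an egg reduction rate are planned.
- Resistance is treated separately as detection of helminths at follow-up, in both Sample size and Laboratory analysis, and the sample size reproduces as one for estimating a proportion.
- A reader shown a fall from 50% to 25% would not confuse it with near-complete clearance.

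This largely stands, and it rules out two stronger readings. A reader might infer that the plan cannot measure resistance at all; the failure proportion and related measures are there. A reader might also infer that the plan would declare albendazole effective whenever p < 0.05; no sentence says so.

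A third tempting reading is that the test is equally blind for every species. For Trichuris it is not. I simulated 345 children with 12.5% positive at baseline. At 50% failure the test rejects in about 91% of studies with no new positives, 68% if 1% of baseline negatives turn positive, 42% if 2% do and 3% if 5% do. At 5% failure it rejects in 93% to 100% over that range. Significance can therefore differ between good and poor efficacy, but partly because of new positives, which are not treatment failures.

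Interval methods can fairly be left to an analysis plan that is not shown. The choice of test cannot be treated that way, because the article states it and assigns it the determination of efficacy. The other measures do not repair this as printed, since the cure-rate and egg reduction formulas are wrong.

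**Conclusion.** The point holds in limited form. For any helminth, the endpoint on which the 50% resistance assumption is defined, significance of the named test does not show whether albendazole works adequately or fails in half of infected children: it is reached from 5% failure to about 84%. For Trichuris at 50% failure it is moderate (p about 0.007 to 0.009) and fragile. The defect is the role given to the test, not the absence of effect measures.

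The figures rest on the article's own 50% prevalence, 25% Trichuris share and 50% failure, on 345 children followed, and on no new positives except where a rate is assumed. The data to be collected are unaffected; what needs changing is the basis for the efficacy conclusion.

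**What to change.** 1. Correct the formulas first. Cure rate = baseline positives who are negative at sample 2, divided by baseline positives. Egg reduction = 1 − (mean post / mean pre). Multiply each by 100.
2. For each species, base the efficacy and resistance conclusion on the failure (or cure) proportion at sample 2 among children positive for that species at baseline, and on the egg reduction rate, each with a 95% confidence interval. A Wilson interval suits the proportion, and a bootstrap over children suits egg reduction.
3. Keep the before/after prevalence change as a descriptive figure, and drop the wording that makes its p-value the determination of efficacy.
4. The local egg reduction estimates in the Background (99.8% for Ascaris, 93.6% for hookworm, 72.7% for Trichuris) may be cited as context. They should not serve as an adequacy threshold, because the same section describes albendazole alone as apparently inadequate, above all for Trichuris.

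Cost: revised wording and a few lines of code, with no further data. The conclusion becomes an interval instead of a single p-value, and for Trichuris that interval will be wide.

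### Before/after and four-visit prevalences from the same children are tested with the Yates chi-square for independent groups: p-values are too large, with little effect at the plan's own values but large effects for species with low cure, low prevalence or new positives

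*Protocol article*

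**What the plan says.** The Study design section describes one group followed over time: "Prospective cohort study of children aged 2 to 11 years, with an individual time of participation of 4 and a half months". There is no control group. On egg counting, Laboratory analysis states: "This procedure will be performed on the 4 samples per subject collected throughout the study".

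Statistical analysis names the test for these repeated samples twice. For efficacy, "the prevalence will be measured before and after receiving treatment and compared using the Yates chi-square test". For the visits, "Comparisons will also be made between sample 1, sample 2, sample 3 and sample 4 to determine the positivity" of each parasite species, "using the Yates chi-square test, setting a significance level of p < 0.05".

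The same section lists chi-square, Fisher and Wilcoxon tests "to compare frequencies between groups". The only paired method it names is the "t-test for paired samples", reserved for qPCR cycle thresholds. No paired or repeated-measures method is named for a positive/negative result.

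**The concern.** Sample 1 and sample 2 of a child are a matched pair. The information on change lies in the children whose status changes: those who clear an infection and those who become positive. A test for independent groups uses only the two marginal prevalences and takes the covariance between visits as zero. If children positive at one visit tend to be positive at the next, that covariance is positive, so the assumed variance is too large and the p-value too high.

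The Yates correction also belongs to a 2×2 table. Four visits can be compared with it only as up to six pairwise tests per species, each with the same fault.

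At stake is a real but partial decline in one species being reported as no significant reduction, in a study whose first major outcome is albendazole resistance.

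**Working it through.** **Plan's own figure.** Sample size gives a population of 3379, 50% helminth prevalence and 10% loss. The margin is not stated; 5 points is assumed here. With the finite-population formula n = N·p(1−p) / [(d²/z²)(N−1) + p(1−p)]:

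3379 × 0.25 / [(0.0025/3.8416) × 3378 + 0.25] = 844.75 / 2.448 = 345.0, and 345.0 × 1.10 = 379.5, rounded up to 380.

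The age strata under Recruitment of participants also sum to 345. So 380 is a precision calculation and does not depend on the Yates test. The checks below use n = 345 pairs. Using 380 × 0.90 = 342 moves the results by no more than about one percentage point.

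**Planning values.** Any helminth is 50%; Trichuris is 0.50 × 0.25 = 12.5%, or 43 of 345. Resistance is 50%, so 50% of positives clear. New-positive rates and other cure rates are assumptions.

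**Formulas.** Let x1 and x2 be the positives at the two visits, b the number cleared and c the number newly positive.
- Yates, as planned: X² = 2n(|x1 − x2| − 1)² / [(x1 + x2)(2n − x1 − x2)], 1 df.
- Exact McNemar: two-sided binomial test of b against c with probability 0.5.

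**Single tables, n = 345**

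| Comparison | b, c | Yates X² | Yates p | Exact McNemar p |
|---|---|---|---|---|
| Any helminth 172 to 86 | 86, 0 | 690·85²/(258·432) = 44.73 | 2×10⁻¹¹ | below 10⁻²⁰ |
| Trichuris 43 to 22 | 21, 0 | 690·20²/(65·625) = 6.79 | 0.009 | 1×10⁻⁶ |
| Trichuris 43 to 30 | 13, 0 | 690·12²/(73·617) = 2.21 | 0.137 | 2·0.5¹³ = 0.00024 |
| Trichuris 43 to 28 | 21, 6 | 690·14²/(71·619) = 3.08 | 0.079 | 0.006 |
| Two follow-up visits, 86 to 106 (illustrative) | 10, 30 | 690·19²/(192·498) = 2.61 | 0.107 | 0.002 |

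The first two rows are the plan's own values, and the conclusion stands under either test. In the last three it reverses.

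The third row shows the mechanism. The standard error assuming independence is √[(0.1246·0.8754 + 0.0870·0.9130)/345] = 0.0234. The paired one is √[(0.0377 − 0.0377²)/345] = 0.0103. The planned test therefore works with a standard error about 2.3 times too large.

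**Simulated power, two-sided 5%**

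| Prevalence | Cure | New positives among negatives | Yates | Exact McNemar |
|---|---|---|---|---|
| 50% (plan) | 50% (plan) | 0 | 100% | 100% |
| 12.5% (plan) | 50% (plan) | 0 | 91% | 100% |
| 12.5% | 64.5% | 0 | 99.8% | 100% |
| 12.5% | 30% | 0 | 13% | 99% |
| 12.5% | 30% | 1% | 3.5% | 65% |
| 12.5% | 50% | 2% | 41% | 82% (81 to 82% at n = 342) |
| 5% | 50% | 0 | 21% | 86% |

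**Simulated type I error of Yates at nominal 5%.** With equal prevalence at both visits and 60% or 80% of positives persisting: 2.4% and 0.1% at 50% prevalence; 0.2% and below 0.01% at 12.5% prevalence. With no within-child correlation it is about 4%.

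**The case against.** The strongest reply is that the choice of test hardly matters where the plan has committed itself. At its planning values Yates has full power for any helminth and loses about 9 points for Trichuris. At 64.5% cure, the top of the range cited in the Background, nothing is lost. That stands. A reader might infer from the 30% cure rows that power is largely lost throughout; the documents do not support so general a claim. Those rows rest on assumed cure and new-infection rates. They are plausible, because the cited Trichuris cure range is 2.6 to 64.5% and reinfection is itself a major outcome, but they are not the plan's.

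The error is also conservative. A reader might fear false claims of efficacy, but under positive correlation false positives fall. Nor is this the only efficacy measure: cure rate and egg reduction rate are also planned, and the choice of test does not alter them. Rejecting no change would not settle resistance either: in the 43 to 30 table McNemar gives p = 0.00024 while 30/43 = 70% of infected children remain positive.

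Household clustering may also be suspected, because the sweep under Recruitment of participants states no limit of one child per home. But the article does not say that siblings are enrolled, and McNemar would not correct for that clustering.

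Finally, Yates might have been meant as a continuity-corrected McNemar. Nothing in the text says so.

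None of this makes the planned p-value valid for paired data.

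**Conclusion.** The mismatch is real and is fixed in the text: a test for independent groups is assigned to paired and repeated results from the same children. The p-values are wrong in a known direction, too large, provided results within a child are positively correlated.

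The practical size depends on the species. At the plan's own values, with no new positives, conclusions hardly change. For a species with lower cure, lower prevalence or some new positives, half or more of the power can go and a conclusion can reverse. The same is probable for contrasts between follow-up visits. These larger losses depend on the assumed rates shown.

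Neither a general loss of power nor a fault in the sample size of 380 follows from this.

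**What to change.** For sample 1 versus sample 2, replace the Yates chi-square with McNemar's test per species, in its exact form when discordant pairs are few. Report the paired risk difference with its 95% confidence interval.

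For the four visits, use one GEE or mixed logistic model per species, with child as the repeated unit and visit as a factor. Cluster on household only if a household identifier is recorded; the article does not mention one.

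State that contrasts after sample 2 reflect reinfection mixed with the re-treatment of positive children described under Albendazole treatment and clinical follow-up. The model corrects the variance but does not separate the two.

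The cost is analysis wording. The methods are standard in Stata, and no new data or change of sample size is needed.
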